**Schedule of Assessment**

| **Study measures and Procedures** | **Time Point** | | | | | | | |  |
| --- | --- | --- | --- | --- | --- | --- | --- | --- | --- |
| **Baseline** | **Wk1** | **Wk2** | **Wk3** | **Wk4** | **Wk5** | **Wk6** | **3m FU** | **6m FU** |
| Consent | X |  |  |  |  |  |  |  | X |
| Screening | X |  |  |  |  |  |  |  |  |
| Demographics/medical history | X |  |  |  |  |  |  |  |  |
| IPAQ | X |  |  |  |  |  |  | X |  |
| Weight | X | X | X | X | X | X | X | X | X |
| BMI | X |  |  |  |  |  |  |  |  |
| Blood Lipid profile | X |  |  |  |  |  |  | X |  |
| Blood pressure | X |  |  |  |  |  |  | X | X |
| TRE instructions | X |  |  |  |  |  |  |  |  |
| Concurrent medication/comorbiidities | X |  |  |  |  |  |  | X |  |
| TRE Adherence |  | X | X | X | X | X | X | X | X |
| Feedback/ratings |  | X | X | X | X | X | X | X | X |

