**Secondary Outcomes**

- Changes in weight from baseline to 6 weeks, and to 3 months and 6 months.
- Changes in blood pressure from baseline to 3 months and 6 months,
- Changes in lipid profile from baseline to 3 months;
- Participant feedback and ratings of the intervention, including the helpfulness of the intervention, recommending it to friends, readiness to continue, barriers and facilitators, and most popular 8-hour time frames.
- Changes in ratings of the difficulty adhering to TRE and ratings of hunger over time
- Estimates of effect size for future randomised trials, if TRE is deemed feasible and efficacy is encouraging.
- Comparison of weight changes in TRE to weight changes in other weight-loss cohorts in our previous trials and community clinics.

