**TRE intervention**

Participants will be asked to consume all their food during an 8 hour period each day for the next three months. Over the remaining 16 hours each day, participants can drink, but only non-calorie drinks (e.g. water or coffee/tea with no milk or sugar). Participants will be free to choose which 8-hour period they would like to eat in.

**Follow-up visits and calls:** Participants will attend at one and six weeks, to provide measures of weight and to discuss their progress. They will also receive phone calls at weeks 2, 3, 4 and 5, that will monitor progress and collect data on adherence.

**12 week follow-up visit**: Participants will attend at 12 weeks to provide measures of weight and blood pressure, and a blood sample for lipid profile and to report on their adherence to TRE and provide TRE ratings.

**Final follow up visit:** Participants will attend at 6 months to provide measures of weight and blood pressure, and to report on their adherence to TRE and provide the final TRE ratings.

Participants will receive £10 at the 6, 12 week and 6 month visits as a compensation for their time and travel. Participants providing a blood sample at baseline and 12 weeks, will also receive £10 for each sample given.

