***Final follow up at 6 months:***

- Weight
- Blood Pressure
- Number of weeks on which TRE was adhered to
- 8-hour time periods selected.
- Ratings of TRE helpfulness, TRE difficulty, ratings of hunger on days TRE was adhered to

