# DATA HANDLING AND RECORD KEEPING

**Confidentiality**

Only study personnel and the study sponsor will have access to study data. We will not request any information about participants from their doctors.

Participants will not be identifiable from their study data. They will be assigned a participant ID number. Study data will be collected on paper CRFs, and will contain the participant ID only. Patient identifiable data will be entered onto a spreadsheet, for the purposes of contacting participants throughout the study. This data will be kept securely, and separately to the CRFs. The spreadsheet will be password protected and held on an encrypted USB stick. When not in use, the USB will be stored in a locked drawer. Original paper copies will be filed and kept in a locked cabinet. Only study staff will have access to the USB and paper copies.

All information will be kept confidential. Copies of all documents regarding the study will be kept in the trial master file (TMF) and/or relevant site file.

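### Blood pressure change to 6 months is an outcome, but medication is not recorded at 6 months, so blood-pressure drug changes first made after the 3-month visit go unseen

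*Protocol*

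**What the plan says.** The protocol's Secondary Outcomes section lists "Changes in blood pressure from baseline to 3 months and 6 months". The 6-month measurement is confirmed in the Study Scheme Diagram, in the Schedule of Assessment, in the 6-month list under Measures, and in the visit description under TRE intervention: "Participants will attend at 6 months to provide measures of weight and blood pressure, and to report on their adherence to TRE".

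The Schedule of Assessment also has a row "Concurrent medication/comorbiidities". It is ticked at baseline and at the 3-month follow-up. Its 6-month cell is empty. Neither the 6-month list under Measures nor the 6-month visit description names medication.

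The Confidentiality section closes one other route to the information: "We will not request any information about participants from their doctors".

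The Study Design section describes a single cohort followed over time. Statistical Analysis applies a paired t-test to the change in blood pressure from baseline to follow-up. Inclusion Criteria admit people with a BMI over 28 if they have comorbidities, and the only drug class named under Exclusion Criteria is psychiatric medication.

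**The concern.** With no concurrent control, a change in blood-pressure drugs is an obvious competing explanation for a before-after change in blood pressure. It can act either way: a newly started drug looks like benefit, and a stopped drug hides it. Participants may well be taking such drugs, since comorbidity is one route into the study.

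The schedule pairs a medication record with drug-sensitive cardiovascular measurements at baseline and 3 months. The 6-month blood pressure is the one such measurement without that pairing. This is a matter of data collection. A statistical analysis plan can decide how to use medication data, but it cannot supply data that no visit collects. At stake is whether the 6-month blood pressure result can be checked before it is reported, or used among the effect estimates that Secondary Objectives intends for a future randomised trial.

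**Working it through.** **Step 1: compare the schedule rows.** The Schedule of Assessment has nine time points: baseline, weeks 1 to 6, 3 months and 6 months.

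| Row | Ticked at |
| --- | --- |
| Blood pressure | Baseline, 3 months, 6 months |
| Lipid profile | Baseline, 3 months |
| Concurrent medication and comorbidities | Baseline, 3 months |

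Lipids and 3-month blood pressure have a matching medication record. Blood pressure at 6 months does not.

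**Step 2: compare with the text.** The 6-month list and visit description omit medication. This is weak corroboration, because the baseline and 12-week lists under Measures omit it too, although the schedule ticks it at those visits. The finding therefore rests on the schedule, with nothing elsewhere in the protocol to contradict it.

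**Step 3: define the gap.** A drug change made by 3 months and still in place is captured by comparing the 3-month record with baseline. What is lost is any change first made between 3 and 6 months.

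**Step 4: gauge the size.** There is no stated figure to reproduce: Sample Size gives a pragmatic 50, with no SD, effect or error rate. All inputs below are assumptions.

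- f, the share of participants who change blood-pressure drugs between 3 and 6 months: 5–10%
- d, the shift in systolic pressure per changer: 5–10 mmHg, all in one direction
- n, pairs at 6 months: 45; SD of change: 12 mmHg; two-sided 5% test

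Shift in the mean = f × d:
- low: 0.05 × 5 = 0.25 mmHg
- high: 0.10 × 10 = 1.0 mmHg

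Standard error = 12/√45 = 1.789 mmHg. Half-width of the 95% interval = t(0.975, 44) × 1.789 = 2.015 × 1.789 = 3.6 mmHg.

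Shift relative to half-width: 0.25/3.605 = 7%; 1.0/3.605 = 28%.

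Rejection rate when the only true change is the drug shift, from the noncentral t distribution with 44 degrees of freedom:
- noncentrality 0.25/1.789 = 0.14 gives 5.2%
- noncentrality 1.0/1.789 = 0.56 gives 8.5%

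**Step 5: vary the assumptions.** With all 50 participants, the half-width is 2.8 mmHg at SD 10 and 4.3 mmHg at SD 15, so a 1.0 mmHg shift is 35% or 23% of it. With 30 pairs and SD 12, the half-width is 4.5 mmHg and the same shift is 22% of it. If as many as 20% changed drugs in this one interval, by 10 mmHg each and all in one direction, the shift would be 2.0 mmHg, or 55% of the 3.6 mmHg half-width, with 19% rejection. That is an extreme case. Changes in mixed directions shrink every figure here.

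**The case against.** The strongest reply is that little depends on this. The primary objective is feasibility, through adherence and retention, and blood pressure is one of several secondary outcomes in an exploratory pilot of 50. TRE is asked for over three months, so the 6-month reading falls after the prescribed period. Without a control group, that change could not be credited to TRE even with a complete drug history, since regression to the mean, season and other changes in behaviour remain. On plausible inputs the shift is smaller than the sampling error. All of this stands, and it sets the severity.

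A reader might infer that drug changes cannot be separated from the blood pressure result at any time point. The documents do not support that: medication is recorded at 3 months, so the 3-month blood pressure and lipid outcomes have what they need. How those records are used in analysis can be left to a statistical analysis plan. For the same reason, the size should not be worked out from all drug changes since baseline.

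A reader might also infer that the missing information is beyond recovery. That is too strong. The Confidentiality section bars requests to doctors, not questions to participants, who attend in person at 6 months. The accurate statement is that the plan as written does not ask them.

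None of this removes the gap. Followed as written, the schedule leaves drug changes between 3 and 6 months unrecorded for a stated outcome.

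**Conclusion.** The point holds in a narrow form: one outcome (change in blood pressure from baseline to 6 months) and one interval (drug changes first made after the 3-month visit). The schedule facts are certain. The size, 0.25–1.0 mmHg and a rejection rate of at most about 8.5% in the main scenario, rests wholly on assumed rates, effects, direction, retention and SD, and shows only the order of magnitude. Severity is minor. It is worth acting on because the remedy is cheap and works only if it is in place before the 6-month visits. It removes one identifiable competing explanation and does not turn an uncontrolled change into an effect of TRE.

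**What to change.** 1. In the Schedule of Assessment, tick the concurrent medication and comorbidities row at the 6-month follow-up.
2. Add the same item to the 6-month list under Measures. While doing so, reconcile the baseline and 12-week lists, which omit an item that the schedule requires at those visits.
3. Report the 6-month blood pressure change in all participants as the main result, with a sensitivity analysis excluding those whose blood-pressure drugs changed since baseline.

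The cost is one existing question repeated at an existing visit, and one extra line in a table. The sensitivity analysis will have fewer participants and may be a selected group, because weight loss can itself prompt a drug change. Excluding those participants could remove some who responded, so the all-participant result should stay primary and the restricted one should be read only as a check.

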**End of Study Definition**

The study would be completed and the REC informed after the final attempt to collect 6-month follow-up data from the last participant.

# STATISTICAL CONSIDERATIONS

**Sample Size**

In this early phase exploratory research, we opted for a pragmatic sample size of 50, achievable economically and quickly, but large enough to provide reasonable confidence intervals on key estimates.

**Statistical Analysis**

Descriptive statistics will be used to report on proportions of participants adhering to TRE; the 8-hour time frames most commonly selected; and client feedback ratings. Paired samples t-test will be used to examine any significant changes from baseline to follow-up in weight, BMI, blood pressure, and blood lipid profiles.

Adherence rates to TRE and weight/BMI changes will be compared against previous weight-loss intervention cohorts (e.g. our previous trials, community weight clinic), via Chi-square analysis for categorical variables and ANOVA for continuous variables.

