**Study Scheme Diagram**

| **Recruitment**  Potential participants contact the study team via phone/email after seeing study ads and are screened. If eligible, they receive appointment and are sent the Participant Information Sheet (PIS). | | | | | | | |
| --- | --- | --- | --- | --- | --- | --- | --- |
|  |  | | |  | |  |  |
| **Baseline visit**  Informed consent; baseline questionnaires and measures of weight, BMI, blood pressure (BP) and lipid profile. TRE instructions given. | | | | | | | |
|  | |  |  |  |  | |  |
| **Week 1 Visit:** Participants will attend the clinic to give their weight and report on progress. | | | | | | | |
|  | | | |  | | | |
| **Weeks 2 to 5 Phone calls:** Participants will be called to check on their progress, and to collect data on self-reported weight and adherence. | | | | | | | |
|  | | | |  | | | |
| **Week 6 Visit:** Participants will attend the clinic to give their weight and report on their progress. | | | | | | | |
|  | | | |  | | | |
| **Week 12 visit:** Participants will attend the clinic to report on their progress. Measures of weight, BP, and limpid profile will be taken | | | | | | | |

**6 month follow up visit:** Participants will attend the clinic to give their weight, BP and report on their progress.

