***Weekly:***

- Weight (Week 1 and 6 only)
- Number of days on which TRE was adhered to
- 8-hour time periods selected.
- Ratings of TRE helpfulness, TRE difficulty, ratings of hunger on days TRE was adhered to
- Comments on TRE barriers and facilitators (Week 1 and 6 only)

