**Subject withdrawal**

Participants will be able to stop the TRE intervention at any time. Participants who stop the intervention will be followed up at 6 weeks and 3 months, unless they do not wish to be.

Unless withdrawn participants request otherwise, data collected up to the point of their withdrawal will be used in the study analysis. Withdrawn participants will not be replaced.

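### Paired t-tests for weight change use only people weighed at each visit, so weights collected before a missed visit add nothing to the 3- and 6-month estimates

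*Protocol*

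**What the plan says.** The Statistical Analysis section names one within-cohort method for all the physiological measures: "Paired samples t-test will be used to examine any significant changes from baseline to follow-up in weight, BMI, blood pressure, and blood lipid profiles". It states no imputation step. The Secondary Outcomes list "Changes in weight from baseline to 6 weeks, and to 3 months and 6 months", so the test would be applied at three time points for weight.

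The Subject withdrawal section says that, unless the participant asks otherwise, "data collected up to the point of their withdrawal will be used in the study analysis". It adds "Withdrawn participants will not be replaced", and on people who stop eating within the window: "Participants who stop the intervention will be followed up at 6 weeks and 3 months, unless they do not wish to be". It does not name 6 months.

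Weights are also collected between baseline and 3 months. The Weekly list under Measures gives weight at weeks 1 and 6, which are clinic visits. For weeks 2 to 5 the Study Scheme Diagram has "Participants will be called to check on their progress, and to collect data on self-reported weight and adherence".

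The Sample Size section reads "we opted for a pragmatic sample size of 50, achievable economically and quickly", without a dropout rate or a standard deviation. The Primary Outcome section defines drop-out as not attending the 3-month session and reports it as an outcome.

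**The concern.** A paired t-test needs both members of the pair. Without imputation, the 3-month test covers people weighed at baseline and at 3 months, and the 6-month test people weighed at baseline and at 6 months. A participant seen at baseline, week 1 and week 6 and then lost has shown how the weight was moving, yet that information does not enter either later estimate.

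This matters if attendance is related to weight loss. If people who have lost little are likelier to stay away, those who attend are a favourable selection. Weight change is secondary here, but the result has two further uses: the comparison with previous weight-loss cohorts, and effect-size estimates for a future randomised trial. An overstated loss would carry into both. The exposure may be greatest at 6 months, where the withdrawal section does not mention follow-up of people who stopped the intervention.

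**Working it through.** **Nothing to reproduce.** The sample size of 50 is pragmatic and has no inputs. The protocol gives no expected dropout, weight change, SD or correlation, so everything below except n = 50 is assumed.

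**1. Numbers in the test.** With a proportion d missing, n = 50 × (1 − d): 40 at 20% and 35 at 30%. The 95% CI half-width is t(0.975, n − 1)/√n in SD units: 0.28 at n = 50, 0.32 at n = 40 and 0.34 at n = 35.

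**2. Overstatement without a model.** Let r be the ratio of the non-attenders' mean change to the attenders'. The attenders' mean overstates the whole-cohort mean by 1/((1 − d) + d·r).

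| Missing d | r = 1 | r = 0.5 | r = 0 |
|---|---|---|---|
| 20% | 1.00 | 1/0.90 = 1.11 | 1/0.80 = 1.25 |
| 30% | 1.00 | 1/0.85 = 1.18 | 1/0.70 = 1.43 |

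**3. What week 6 can recover.** Assume a true 12-week change of mean -2.5 kg (SD 3.5), a week-6 change of mean -1.5 kg (SD 2) and a correlation of 0.8. The regression slope of 12-week on week-6 change is 0.8 × 3.5/2 = 1.4. Missingness at week 12 rises with smaller week-6 loss, at the log-odds per kg shown. Means are over simulated trials of n = 50 (4,000 datasets).

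| Missing | Log-odds per kg | Attenders' mean (kg) | Overstatement |
|---|---|---|---|
| 20% or 33% | 0 | -2.5 | none |
| 20% | 0.3 | -2.81 | 0.31/2.5 = 12% |
| 20% | 0.6 | -3.06 | 0.56/2.5 = 22% |
| 33% | 0.2 | -2.83 | 0.33/2.5 = 13% |
| 33% | 0.3 | -3.01 | 0.51/2.5 = 20% |
| 33% | 0.6 | -3.37 | 0.87/2.5 = 35% |

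In each row, predicting from week 6 gives about -2.5 kg. The last row shows why. An excess of 0.87 kg at week 12 corresponds to attenders being 0.87/1.4 = 0.62 kg ahead at week 6. That lead can be seen because the non-attenders were weighed then, and subtracting 1.4 × 0.62 = 0.87 kg restores -2.5 kg.

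Precision is not sacrificed. In the last row the empirical standard error is 0.56 kg using week 6 against 0.58 kg for attenders. With 33% missing and dropout unrelated to weight it is 0.54 against 0.61 kg.

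**4. A less favourable mechanism.** The set-up in step 3 suits the correction, because dropout depends only on a weight that was observed. When dropout depends instead on the unseen 12-week change, one scenario gives an attenders' mean of -3.52 kg and a week-6 estimate of -2.92 kg. The bias falls from 1.02 to 0.42 kg, so 0.60/1.02 = 59% is removed and the rest remains.

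**5. The other measures.** Lipids are taken only at baseline and 12 weeks, so no interim value can be borrowed. Blood pressure is taken at baseline, 12 weeks and 6 months, so a model can help only at 6 months, for people seen at 12 weeks.

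**The case against.** The strongest reply is that the protocol names a test, not an analysis set. A paired t-test can be run after imputation, and the missing-data rule may sit in a statistical analysis plan that is not at hand. That stands as far as it goes: a reader might infer that the protocol commits itself to an analysis of completers, and it does not say so. People who stopped the intervention but attended are also in the test, so the set is attenders at the visit, not completers of the intervention.

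A reader might also infer that the test contradicts the withdrawal rule. It does not. Someone lost after week 6 still counts in the 6-week weight change and in the adherence summaries, so earlier data are used somewhere in the analysis. Nor does the test conflict with the aim of reasonable confidence intervals, since a paired t-test supplies one.

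It is fair, too, that the direction and size of any bias cannot be derived from the protocol, that weight is secondary in a feasibility pilot, and that drop-out will be reported so readers can see it.

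What the reply does not remove is that the paired test is the only within-cohort method fixed for weight change. Reporting drop-out shows that people are missing but does not correct the estimate, and the weights that could help are already being collected.

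**Conclusion.** The point holds as a poor choice of method for the 3- and 6-month weight changes. As written, the paired test estimates change among attenders and leaves out earlier weights of people who miss the visit.

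It does not support the statement that reported weight loss will be biased. Overstatement arises if poorer losers are likelier to stop attending; if attendance is unrelated to weight, there is none. Under the assumed inputs, with 20-33% missing and dropout depending at most on week-6 weight change, the attenders' mean lies between -2.5 and about -3.4 kg for a true -2.5 kg. Using week 6 brings it back to about -2.5 kg at equal or better precision. If dropout depends on weights never seen, the correction is partial. The change is worth making because it is cheap and needs no new data; the primary adherence outcome is unaffected.

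**What to change.** In the Statistical Analysis section and the synopsis, replace the paired t-tests for weight with a repeated-measures mixed model that includes all participants and all clinic-measured weights (baseline, weeks 1, 6 and 12, and 6 months). Report mean change with a 95% CI at 6 weeks, 3 months and 6 months. State the covariance structure in advance, with a simpler fallback: an unstructured matrix over five visits has 5 × 6/2 = 15 parameters, which is a lot for 50 people.

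Add a sensitivity analysis with missing weights set to baseline, labelled as conservative. In the 33%, 0.6 log-odds example it gives about -2.25 kg against a true -2.5 kg.

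Keep the paired attenders' results as supportive, and use them in the cohort comparison where the historical cohorts were analysed that way, so that like is compared with like. Paired tests may stay for lipids. For blood pressure the model is optional, with a gain only at 6 months.

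The cost is revised wording, slightly more analysis work in standard software, and possibly a smaller reported weight loss.

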# SUMMARY/SYNOPSIS

| **Short Title** | TRE |
| --- | --- |
| **Methodology** | Cohort Follow-up |
| **Research Sites** | 1. Queen Mary University of London  Health and Lifestyle Research Unit  [name]  London  [name] |
| **Objectives**  **/Aims** | Time-restricted eating (TRE) allows food intake during a period of eight hours each day. TRE showed promising results in animal studies and become popular with dieters. This is a pilot study to assess its acceptability and short-term effects by examining 1. Client adherence compared with other methods used with similar clients; 2. Weight loss compared with other methods used with similar clients; 3. Changes in heart risk factors; 4. Whether it would be worth conducting a bigger, controlled trial. |
| **Number of Participants/Patients** | 50 |
| **Main Inclusion Criteria** | - aged over 18 years, - BMI over 30kg/m2, or over 28kg/m2 with comorbidities - Speaks, reads, and understands English |
| **Statistical Methodology and Analysis (if applicable)** | Descriptive statistics will be used to report on the proportion of participants adhering to TRE; the 8-hour time frames most commonly selected; and client feedback ratings. Paired samples t-test will be used to examine any significant changes from baseline to follow-up in weight, BMI, blood pressure, and blood lipid profiles. Adherence rates to TRE and weight/BMI changes will be compared against previous weight-loss intervention cohorts (e.g. our previous trials, community weight clinic), via Chi-square analysis for categorical variables and ANOVA for continuous variables. |
| **Proposed Start Date** | Grant: November 2017  Recruitment: February 2018 |
| **Proposed End Date** | Recruitment: May 2018  Grant: November 2018 |
| **Study Duration** | 18 months (3m for set-up; 3m for recruitment; 6m for final follow-ups; 3m for write-up and study close) |

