**Primary Outcome**

The primary outcome is the adherence to TRE over a period of 3 months, specifically the average number of days on which TRE was adhered to. We will also monitor the retention rates at 6 weeks, three months and 6 months, defined as the proportion of participants who adhere to TRE at least once a week; and the drop-out rate defined as the proportion of participants who do not attend the 3 month follow-up session. We will compare retention and drop-out rates with those in our previous trials and community clinics.

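### The cohort comparison names ANOVA and chi-square over several earlier cohorts but no TRE-versus-cohort difference, so on its most natural reading it does not isolate TRE

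*Protocol*

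**What the plan says.** The question is always TRE against something else. The Synopsis lists as an aim "Weight loss compared with other methods used with similar clients". Secondary Outcomes lists "Comparison of weight changes in TRE to weight changes in other weight-loss cohorts in our previous trials and community clinics". Primary Outcome adds, for the attendance and persistence measures, "We will compare retention and drop-out rates with those in our previous trials and community clinics". Nowhere does the protocol ask whether the earlier cohorts differ among themselves.

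The method is given under Statistical Analysis and repeated in the Synopsis. TRE results are to be "compared against previous weight-loss intervention cohorts (e.g. our previous trials, community weight clinic), via Chi-square analysis for categorical variables and ANOVA" for continuous ones. The comparators are plural and given only as examples. Their number, sizes and results are not stated. No contrast, pairwise step or pooling of comparators is named.

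Under Sample Size, 50 participants is a pragmatic choice, described as "large enough to provide reasonable confidence intervals on key estimates".

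**The concern.** With three or more groups, one-way ANOVA and the k × 2 chi-square test the hypothesis that all groups share one mean or one proportion. The protocol asks a narrower question: does TRE differ from the others? The two questions can part in both directions.

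- Research trials and a routine clinic may differ in weight loss and drop-out for reasons unrelated to TRE. That alone can make the omnibus test reject.
- If the earlier cohorts are alike and only TRE differs, the omnibus test spends degrees of freedom on differences nobody asked about.

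In neither case does the test yield an estimated TRE-minus-comparator difference, which is what a decision about a larger trial could use. The issue is separate from confounding between cohorts: it would remain with well-matched cohorts.

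**Working it through.** The protocol has no figure to reproduce, because it states no alpha, power, SD, effect size or comparator size. Only the TRE sample size of 50 comes from the document. Everything else here is assumed: two-sided 5% level, SD of weight change 4 kg, and two earlier cohorts of n₁ and n₂ patients whose true means differ by d.

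**Step 1. Omnibus ANOVA when TRE sits at the weighted mean of the earlier cohorts.** The noncentrality is λ = Σ nᵢ(μᵢ − μ̄)²/σ². TRE lies at the grand mean and contributes nothing, so λ = [n₁n₂/(n₁+n₂)] · d²/σ². The rejection probability is the upper tail of the noncentral F distribution with 2 and N − 3 degrees of freedom, beyond its 5% critical value.

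Examples:
- 50 + 50, d = 1 kg: λ = 25 × 1/16 = 1.56; critical F(2, 147) = 3.06; rejection 18%.
- 100 + 300, d = 2 kg: λ = 75 × 4/16 = 18.75; critical F(2, 447) = 3.02; rejection 98%.

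| Earlier cohorts | d = 1 kg | d = 1.5 kg | d = 2 kg |
|---|---|---|---|
| 50 + 50 | 18% | 36% | 59% |
| 100 + 100 | 33% | 65% | 89% |
| 100 + 300 | 47% | 83% | 98% |

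A single contrast of TRE against the size-weighted combined comparators has true value zero here and rejects in 5% throughout. When d = 0 the omnibus test also rejects in 5%.

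**Step 2. Drop-out by chi-square (simulation).** With earlier cohorts at 20% and 35% and TRE at their pooled rate, the 3 × 2 chi-square rejects in about 30%, 56% and 73% for the same three pairs of sizes. TRE against the pooled comparators rejects in about 5%.

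**Step 3. Power when only TRE differs.** TRE is shifted by 1.75 kg and the comparators are equal, with 100 patients each.

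| Comparators | Omnibus F | TRE contrast |
|---|---|---|
| 1 | 71% | 71% |
| 2 | 69% | 79% |
| 4 | 63% | 83% |
| 5 | 60% | 84% |

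With one comparator F = t², so the two tests coincide.

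**Step 4. What Step 1 does not show.** If the earlier cohorts differ, TRE cannot equal both. At 100 + 300 with d = 2 kg, the weighted mean is 300 × 2/400 = 1.5 kg above the smaller cohort and 0.5 kg below the larger one. Separate t-tests of TRE against each cohort give at least one significant result in about:

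| Earlier cohorts | d = 1 kg | d = 1.5 kg | d = 2 kg |
|---|---|---|---|
| 50 + 50 | 18% | 30% | 45% |
| 100 + 100 | 22% | 37% | 58% |
| 100 + 300 | 25% | 46% | 69% |

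The omnibus excess over pairwise testing is nil at 50 + 50 with d = 1 kg and clear at larger sizes and gaps.

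**The case against.** The strongest reply is that the protocol does not fix an omnibus test. It says that TRE will be compared against earlier cohorts by a family of tests. It does not say that all cohorts enter one test, or that the global p-value is the result to be read. Pairwise tests, one pooled historical group, or ANOVA followed by planned contrasts would all fit, and contrasts are often left to an analysis plan, which is not shown here. This stands in part. A reader might infer that the planned comparison definitely is an all-cohort test; the text supports that only as its most natural reading. What remains is that the method actually named, applied to plural cohorts, does not answer the protocol's own question unless something is added.

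A reader might also take the Step 1 percentages as false-positive rates for TRE. They are not. TRE matches only the average of the earlier cohorts and truly differs from each of them, so pairwise tests reject often as well. The 5% benchmark belongs to the single combined contrast, not to cohort-by-cohort comparison.

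Finally, the stakes are limited. This is a single-arm exploratory pilot ("we opted for a pragmatic sample size of 50, achievable economically and quickly"), the primary outcome is the average number of adherent days, and no decision rule uses this p-value. The protocol does mention confidence intervals and effect-size estimates, although it does not tie either to the TRE-minus-cohort difference. That argument stands, and it sets the weight of the point.

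**Conclusion.** The point holds as a minor one. The protocol asks how TRE compares with earlier cohorts but names tests that, with three or more groups and no contrast, address equality of all cohorts and give no TRE-minus-cohort estimate. Under the assumptions above, the omnibus ANOVA rejects in about 18% to 98% when TRE equals the weighted average of two earlier cohorts, against 5% for one combined contrast. When only TRE differs, the power loss is about 10 points with two comparators (69% against 79%) and 24 with five (60% against 84%).

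These figures are illustrations. The number, sizes and spread of the comparator cohorts, the SD and the position of TRE are all assumed, and the true size cannot be derived from the protocol. If a single pooled comparator is used, the concern disappears.

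**What to change.** In Statistical Analysis, and in the matching Synopsis row, state that the comparison is reported as TRE minus each named earlier cohort: the difference in mean weight and BMI change and the difference in retention and drop-out proportions, each with a 95% confidence interval and labelled exploratory. If one overall statement is wanted, specify a single planned contrast of TRE against the combined comparators (for proportions, a two-group comparison with the pooled comparators). Add that an omnibus p-value will not be read as evidence about TRE.

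The cost is a sentence or two of wording, with the same data and software. The downside is several intervals in place of one p-value, which is why the exploratory label and restriction to named cohorts matter.
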